### The online consensus meeting

Professionals and healthcare users who have completed both rounds of the Delphi survey and registered an interest in participating in the consensus meeting will be allocated places based on a first come, first served basis. In the case of the professional stakeholders, efforts will be made to ensure clinicians, researchers and commercial representatives are represented. In advance of the meeting, participants will be asked to vote on whether or not the scope of the consensus meeting should be limited to the outcomes achieving consensus in Round 2 of the Delphi survey.

To minimise screen time during the web-based consensus meeting, participants will be supplied with an overview of the aims of the day and a guidance document outlining the day’s activities. Participants will be asked to complete an online survey identifying their personal top three outcomes from those achieving consensus from the e-Delphi. The purpose of this is to steer both the participants’ thoughts and the conversation in the meeting towards what outcomes are critical. Experienced independent moderators will be recruited to facilitate the consensus meeting discussion to agree a final Core Domain Set. The consensus meeting will be audio-recorded and transcribed to facilitate reporting. These will be classed as source data and will be retained in the study archives, using Unique Identifier Codes for each speaker. Reporting of the Delphi survey will list the outcomes in the final Core Domain Set [22]. The consensus meeting will comprise a plenary stage as well as breakout discussions in which the participants will be allocated to groups along stakeholder lines. The consensus meeting will include anonymised voting on each outcome as either “In” or “Out” which will create histograms and descriptive statistics ‘live’, to be displayed in the meeting. In advance of the meeting, participants will be given materials summarising the anonymised Round 2 results, separately for each stakeholder group. If after two consecutive votes, the consensus criterion is not met for any outcome, they will be dropped in favour of a simple majority criterion, that is, outcomes will be included if more than 50% of participants vote for its inclusion. Because the time for discussion will be limited, there will be no discussion about outcomes that met the criteria for exclusion. In line with the Core Domain Sets resulting from the COMiT’ID study [13], the maximum number of outcomes in the Outcome Domain Set will be seven (adverse effects and up to six further outcomes). Therefore, while the Delphi survey will determine which outcomes are brought to the consensus meeting, if there are more than seven outcomes then the consensus meeting participants will be asked to reduce the number of outcomes. All Delphi survey participants will be invited to agree or disagree with the decisions made at the consensus meeting and these results will be disseminated along with the Core Outcome Domain Set.

### Consensus criteria Delphi survey rounds

Consensus recommendations will be made according to the following definition [27, 28]:Include domain in Core Domain Set: 70% or more of the participants in each stakeholder groups score 7–9, and fewer than 15% score 1–3.Exclude outcome domains in Core Domain Set: 50% or fewer participants in each stakeholder group score 7–9

### Consensus criteria consensus meeting

Consensus from the meeting is defined as 70% or more of the participants agreeing on including one or more outcome domains in the Core Domain Set.

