### Panel size and justification

There is no agreed method to statistically calculate a sample size for Delphi surveys or for consensus meetings and no criteria against which a sample size choice can be judged (e.g. Powell, 2003; Akins et al., 2005). Some individual studies indicate that stakeholder groups of around 20 can provide results that are representative of the views of the wider stakeholder group (Akins et al., 2005). However, one of the key deciding factors is that the participant panel membership should adequately represent their corresponding stakeholder group. Another one is pragmatic. One practical factor that will influence our sample size is the aim of a roughly equal number of participants in each stakeholder group. The consensus meeting will include 20 participants, in line with COMiT’ID [18]. For the Delphi survey and consensus meeting, there will be an equal number of participants from each stakeholder group, or as close as practically possible, and professionals will be balanced across the clinical, academic and commercial sectors.

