To recruit for the consensus meeting, participant information sheets for the survey will inform participants to register their interest in attending the consensus meeting with the research team. Participants will be informed that there are only a limited number of places available. Participants will be reminded after completing the first questionnaire to register for the meeting if they wish to attend. If the required number of participants have not registered following the first questionnaire they will be reminded to register after they completed the second questionnaire. Allocation of places at the consensus meeting will be based on participants who participated in both rounds of the Delphi survey and registered an interest first. The email address and phone number of the Chief Investigator will be available to participants for questions and support. Participants in the consensus meeting will not be screened based on their responses in the survey rounds. Equal participation across stakeholder groups will be encouraged, but if this is not possible, the consensus meeting will go ahead with unequal numbers.

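### The Delphi requires 70% support in each stakeholder group, but the deciding meeting counts all attendees together, under both its 70% rule and its majority fallback, with seats not reserved by group

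*Protocol article*

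**What the plan says.** The Protocol article uses two kinds of consensus rule.

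- **Delphi rounds** (Consensus criteria Delphi survey rounds): a domain is included if "70% or more of the participants in each stakeholder groups score 7–9, and fewer than 15% score 1–3". Round 2 participants are reminded of the same per-group rule.
- **Meeting, main rule** (Consensus criteria consensus meeting): "Consensus from the meeting is defined as 70% or more of the participants agreeing on including one or more outcome domains". There is no group condition.
- **Meeting, fallback** (The online consensus meeting): if two consecutive votes fail to reach the criterion, "outcomes will be included if more than 50% of participants vote for its inclusion". Again there is no group condition.

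On composition, Panel size and justification says "The consensus meeting will include 20 participants" and that "there will be an equal number of participants from each stakeholder group, or as close as practically possible". Recruitment methods says that equal participation is encouraged, "but if this is not possible, the consensus meeting will go ahead with unequal numbers". The online consensus meeting adds that eligible people who registered "will be allocated places based on a first come, first served basis". No section reserves places by group or limits the imbalance.

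Voting is anonymised, In or Out for each outcome. Breakout discussions and the Round 2 summaries are split by stakeholder group. Nothing says that the votes are.

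**The concern.** The stated objectives are to compare and integrate the views of professionals and of people living with tinnitus. The Delphi criterion serves this directly, because neither group can carry a domain over the other. The meeting takes the final decision, and there the condition is absent from both voting rules. Under pooled counting the result depends on how many seats each group holds, and that depends partly on who registers first.

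What is at stake is whether a domain in the final set can be described as supported by both groups. If the poll is anonymous and not tagged by group, this cannot be checked afterwards, so it has to be settled before the meeting.

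**Working it through.** **Inputs from the Protocol article.** N = 20 attendees; planned split 10:10; main rule at least 70% of participants; fallback more than 50% of participants. The document gives no figure for this point that could be reproduced, so the check is exact vote counting, with each outcome voted on separately.

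**Votes needed.** Main rule: 0.70 × 20 = 14. Fallback: more than 0.50 × 20 = 10, so 11.

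**Fewest In votes needed from the smaller group.** If the larger group has a seats and votes In unanimously, the smaller group must supply max(0, 14 − a) under the main rule and max(0, 11 − a) under the fallback.

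| Split | Main rule (14) | Fallback (11) |
|---|---|---|
| 10:10 | 4 of 10 (40%) | 1 of 10 |
| 11:9 | 3 of 9 (33%) | 0 |
| 12:8 | 2 of 8 (25%) | 0 |
| 13:7 | 1 of 7 (14%) | 0 |
| 14:6 | 0 | 0 |

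So at the planned split a domain passes the main rule with 6 of 10 in one group voting Out, and the fallback with 9 of 10 voting Out. One group suffices alone from 14:6 under the main rule and from 11:9 under the fallback.

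**Illustrative probabilities.** The documents give no level of support, so these are assumptions. Let the In votes be X ~ Bin(a, p) in the larger group and Y ~ Bin(20 − a, q) in the other, independent. For a single vote, P(X + Y ≥ 14) and P(X + Y ≥ 11) are:

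| p / q | Rule | 10:10 | 12:8 | 14:6 |
|---|---|---|---|---|
| 0.9 / 0.3 | main | 0.19 | 0.43 | 0.72 |
| 0.9 / 0.3 | fallback | 0.81 | 0.95 | 0.99 |
| 0.9 / 0.5 | main | 0.61 | 0.78 | 0.90 |
| 0.9 / 0.1 | main | 0.01 | 0.07 | 0.43 |
| 0.9 / 0.1 | fallback | 0.34 | 0.81 | 0.97 |

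At 0.9 / 0.3, requiring 70% in each group would give about 0.01 at all three splits. If the smaller group is the one with 90% support and the larger has 30%, the main rule gives 0.07 at 12:8 and 0.02 at 14:6. With the same two opinions, the allocation of seats moves the result from 0.02 to 0.72.

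**Which domains can reach the vote.** The Delphi decides what is brought to the meeting, but attendees vote beforehand on whether to stay within the Round 2 consensus outcomes.

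- *Scope kept:* every domain voted on has already had at least 70% scoring 7–9 in each group. The meeting then chooses among jointly supported domains to reach the maximum of seven.
- *Scope widened:* Delphi exclusion requires 50% or fewer scoring 7–9 in each group. A domain at, say, 90% in one group and 30% in the other is neither included nor excluded, and can come to the vote.

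**The case against.** Two stronger readings are tempting, and the document supports neither.

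- A reader might infer that one group can put a domain into the set on its own as the meeting is planned. It cannot. At 10:10 a unanimous group reaches 50%, short of both 14 votes and 11.
- A reader might infer that protection against one-sided domains is lost altogether at the meeting. If the scope is kept to Round 2 consensus outcomes, every candidate has already met 70% in each group.

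The best defence goes further. Pooled voting at a moderated meeting is a legitimate choice, and the Delphi and meeting criteria govern different stages, so they do not contradict each other. There are also mitigations: breakouts by stakeholder group, Round 2 results shown by group, independent moderators, and an invitation to all Delphi participants to agree or disagree, with the results disseminated. A strict per-group rule has a real price too. At 10:10, 4 Out votes in one group would block a domain, against 7 in total under pooling; at 14:6, 2 of the 6 could block it. It would also not help a domain that one group wants unanimously and the other does not, because the support needed from the other group at 10:10 rises from 4 to 7.

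Most of this stands, and it limits the point. It does not answer three things: the scope can be widened by vote, the fallback is pooled and is tipped by an 11:9 split that is compatible with the plan's own wording on balance, and no section has votes recorded by group. The mitigations inform the discussion or report on the result; none changes how votes are counted.

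**Conclusion.** The point holds with conditions. The per-group requirement of the Delphi is not carried into either meeting rule, and the planned equal split is not secured by the way seats are allocated. At 10:10, 6 of 10 in one group can be overridden under the main rule and 9 of 10 under the fallback. Single-group control needs 14:6 or worse under the main rule, but only 11:9 or worse under the fallback, so the fallback is the more exposed of the two.

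The consequence is greatest if the pre-meeting vote widens the scope. If it does not, the effect is on which jointly supported domains survive the cut to seven. The vote counts assume 20 voters and a unanimous larger group. The probabilities rest on assumed support and independent votes, and illustrate how sensitive the result is to the seat split; they do not predict it. The per-group condition is a trade-off, whereas securing balance and recording votes by group is close to free.

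**What to change.** **Main change.** In Recruitment methods and The online consensus meeting, reserve 10 places per stakeholder group, apply first come, first served within each group, and release unfilled places only after a stated registration deadline. Tag the anonymous poll by stakeholder group, and display and report every vote by group. This costs a few sentences and a poll setting, and delivers the balance that Panel size and justification already plans.

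Reserved seats do not cover absences on the day. If one person is missing and the split is 10:9, more than 50% of 19 is 10 votes, and the larger group again carries the fallback alone.

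**Preferably also.** Add a per-group condition to both meeting rules, for example 70% in each group in Consensus criteria consensus meeting and a majority in each group for the fallback. Both need it: if only the main rule were changed, a domain failing it twice would still go to a pooled majority. At 10:10 the conditions would be 7 + 7 and 6 + 6 In votes.

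**Cost of the per-group condition.** Fewer domains pass, and a small group gains a veto if numbers are unequal. With 80% support assumed in both groups, the chance of passing a single 70% vote falls from 0.91 pooled to 0.77 at 10:10 and 0.57 at 14:6. With 90% and 70% support it falls from 0.92 to 0.64 at 10:10. For the fallback at 80% support in both groups, it falls from 0.997 to 0.94 at 10:10. If the study team prefers to keep pooled rules, the reserved seats and the reporting by group should still be adopted, with the choice stated.

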### Data analysis

Reporting of the Delphi survey will fully describe the relevant characteristics of the participants involved at each stage of the Core Domain Set development [22]. Examples of relevant characteristics are gender, ethnic background, socioeconomic status, country and region (e.g. UK (Wales), America (Iowa), France (Paris)), since these factors affect how representative the consensus might be of the target population. There are no special features for the proposed analysis. Descriptive statistics will be computed for scores on each domain (response distributions (%) of participants selecting each of the 1–9 Likert response options).

A designated member of the Study Management Team will analyse numerical data collected in the Delphi survey, using the UoN license for SPSS and Microsoft excel. The data from each round will be subjected to descriptive statistics, such as the distribution of the relevant participant characteristics, distribution of rating scores across each stakeholder group (including the “unable to score” option), and attrition rate from round to round. A separate analysis will assess the shifts in scores across rounds as a consequence of considering the anonymised feedback from other participants. Round 2 score distributions for each outcome domain will be considered at the final consensus meeting using a nominal group technique to evaluate individual perspectives

### Dissemination

Data from the final analysis of the Delphi, and consensus meeting will be presented at relevant national and international conferences, including the British Tinnitus Association and British Society of Audiology meetings. We intend to publish the results of this study in a peer-reviewed journal. This research will be further disseminated to members of the public and clinicians through specialist magazine articles and support groups. In addition, uptake of the Core Domain Set will be actively promoted through deposition in any relevant outcome depositories and informal dissemination within existing professional networks, including via social media channels. Participants will not be identified in any publications.

## Discussion

The purpose of this Delphi study is to establish a Core Domain Set-a list of outcomes that should inform the choice of measurements used when trialling electrical stimulation-based interventions for tinnitus. In order to ensure this Core Domain Set reflects the priorities of all relevant stakeholders, two groups of participants will be recruited: healthcare users and professional stakeholders (including clinicians, researchers, and commercial representatives). The method used to arrive at a Core Domain Set will be an e-Delphi survey, consisting of two online questionnaire rounds, and an online consensus meeting.

This new Core Domain Set would mean that all clinical trials for electrical stimulation-based interventions for tinnitus would use and report the same set of agreed outcomes. Standardised reporting would make comparison between studies easier, especially for meta-analysis and Grading of Recommendations Assessment, Development and Evaluations (GRADE) assessment as part of systematic reviews, improving the clarity on the knowledge produced and the interpretations of the merits of each intervention, leading to improvement in treatments for tinnitus and in turn management of tinnitus patients. In order to comply with GRADE, the final outcome set will be limited to a maximum of seven outcomes.

## Abbreviations

BRC: Biomedical Research Centre
CI: Chief Investigator overall
ENT: Ear, Nose and Throat
GCP: Good Clinical Practice
NIHR: National Institute for Health Research
NHS: National Health Service
PI: Principal Investigator at a local centre
PIC: Patient Identification Centre
PIS: Participant Information Sheet
REC: Research Ethics Committee
R&D: Research and Development department
tACS: Transcranial Alternating Current Stimulation
tDCS: Transcranial direct current stimulation
TMS: Transcranial magnetic stimulation
tRNS: Transcranial random noise stimulation
UoN: University of Nottingham
